## Interim analyses {21b}

No interim analyses will be undertaken.

## Methods for additional analyses (e.g. subgroup analyses) {20b}

Pre-specified hypothesis-generating sub-group analyses, using the variables defined within the minimisation algorithm, will be undertaken using appropriate modelling techniques. These exploratory sub-group analyses will have lower power than the main trial analysis and results will be scrutinised graphically via forest plots.

## Methods in analysis to handle protocol non-adherence and any statistical methods to handle missing data {20c}

With the protocol stating that randomisation should occur after induction of anaesthesia, where possible, and the main data collection time window being only 30 days from surgery, missing data due to withdrawals or lost to follow-up are not anticipated. With efforts to collect full baseline, treatment, and follow-up data on all trial participants, it is thus anticipated that missing data will be minimal. Participants with missing primary outcome data will not be included in the primary analysis in the first instance. However, this presents a risk of bias, and thus consideration will be given to any missing data in the form of a sensitivity analysis to determine the degree to which the conclusions may change with different missing data assumptions. If applicable after investigation into the degree of treatment crossovers, a secondary per-protocol analysis may be undertaken for sensitivity purposes, including only participants who received their randomised intervention.

## Health economic evaluation

A prospectively planned cost-effectiveness analysis will be conducted from an NHS and personal social services perspective, following NICE guidelines [32]. Resource use attributable to neuromuscular blockade reversal during the initial hospital stay will be recorded via CRFs, including length of hospital stay. Community healthcare contacts within 6 months post-surgery will be recorded. Healthcare resource use will be costed using the latest published national reference costs, reflated to the most recent year [33]. Resource use will be reported separately for hospital and community services.

Generic health-related quality of life will be measured using the EQ-5D-5L questionnaire at four time points: baseline, 7 days, 30 days, and 6 months post-intervention. The EQ-5D-5L scores will be converted to health status scores using the UK value set recommended by NICE at the time of analysis [34, 35]. QALYs will be calculated for each participant using the area under the curve (AUC) method, employing the trapezoidal rule to interpolate between time points. Baseline EQ-5D-5L scores will be included to minimise bias in QALY calculations and to adjust subsequent analyses [36, 37]. Whilst more frequent measurements would be ideal, the measurement schedule is necessarily pragmatic within the design of the trial.

A within-trial cost-effectiveness analysis (to 6 months) will be conducted using bivariate regression of costs and QALYs, enabling a probabilistic assessment of incremental treatment cost-effectiveness [38]. Mechanisms of missingness of data will be explored and multiple imputation methods will be applied to impute missing data [39–41]. Imputation sets will be used to estimate incremental cost per QALY estimates and confidence intervals. Findings will be analysed and visualised on the cost-effectiveness plane, as cost-effectiveness acceptability curves, net monetary benefit and value of information analysis. Should costs and quality-of-life not converge within 6 months, more extensive economic modelling using decision-analytic methods may be considered to extend the target population, time horizon and decision context, drawing on best available information from the literature and stakeholder consultations to supplement the trial data. Parameter uncertainty in the decision-analytic model will be explored using probabilistic sensitivity analysis. If longer term decision modelling is to be undertaken, then costs and outcomes will be discounted at 3.5% after the first year of randomisation in line with NICE reference case [32]. All analyses and modelling will be performed using Stata 16 SE (or the latest available version). The study’s economic evaluation reporting will adhere to the Consolidated Health Economic Evaluation Reporting Standards (CHEERS) statement [42].

## Plans to give access to the full protocol, participant level-data and statistical code {31c}

The full trial protocol is available at www.warwick.ac.uk/sinfonia. Research groups requesting the trial dataset and statistical code should include a qualified statistician and initially address the chief investigator, providing a full proposal for their use of the data, for review and approval by the SINFONIA trial management group. The data required for the approved, specified purposes will be provided, after completion of a data sharing agreement. Data sharing agreements will be set up by the sponsors of the trial, the funders, the trial coordination centre, and the trial steering and management groups.

## Oversight and monitoring

### Composition of the coordinating centre and trial steering committee {5d}

The trial is coordinated by the University of Warwick Clinical Trials Unit, who will be responsible for day-to-day management of the trial under the supervision of the Chief Investigator. The Trial Management Group (TMG), consisting of the co-investigators, including public and patient representatives, and project staff involved in the day-to-day running of the trial, will meet at least monthly throughout the project. Significant issues arising from management meetings will be referred to the Trial Steering Committee (TSC), Investigators or Funder, as appropriate.

Trial oversight will be provided by a TSC comprising members of the trial leadership team with a majority of independent clinical researchers, as well as a patient representative. The full remit and responsibilities of the TSC will be documented in a charter which will be signed by all members and which is available on the trial website (www.warwick.ac.uk/sinfonia). The Steering Committee will meet annually or more frequently as required and will take responsibility for major decisions, such as a need to change the protocol for any reason, monitoring and supervising the progress of the trial, reviewing relevant information from other sources, and considering recommendations from the DMC.

## Composition of the data monitoring committee, its role and reporting structure {21a}

A data monitoring committee (DMC) will be appointed comprising two independent clinicians with experience in clinical trials and an independent statistician. The roles of the DMC will include monitoring aggregate data and making recommendations to the TSC on whether there are any ethical or safety reasons why the trial should not continue; advising the TSC regarding the release of data and/or information; and considering data emerging from other related studies. The full remit and responsibilities of the DMC will be documented in a charter which will be signed by all members, and which is available on the trial website (www.warwick.ac.uk/sinfonia).

## Adverse event reporting and harms {22}

The potential risk to trial participants is no higher than that of standard care.

As the study involves a population undergoing surgery and general anaesthesia for major surgery, it is anticipated that many participants will experience events which might be considered adverse events (AEs) or serious adverse events (SAEs). Where such events are secondary outcomes or expected features of the perioperative period, e.g. wound dehiscence or infection, paralytic ileus, venous thromboembolism, anastomotic leak, myocardial infarction, these will be captured on case report forms but will not be reported as AEs/SAEs. All AEs and SAEs will be recorded from the time of IMP administration until 24 h thereafter (over five half-lives of the IMPs).

Where an AE/SAE is considered relevant to the trial by clinical or research teams, it is the responsibility of the site investigator to review all relevant medical records and to record relevant information in the CRF and on the SAE form if applicable. This will include assessment of severity and causality. SAEs will be evaluated for duration and intensity according to the National Cancer Institute Common Terminology Criteria for Adverse Events (CTCAE) Version 5.0.

Once received, an independent causality assessment will be undertaken by the CI or delegate. For any SAEs which are suspected to be caused by the trial intervention by either the CI or site clinician, this will be deemed a Serious Adverse Reaction (SAR), and expectedness will be confirmed by the CI or a delegate with reference to the relevant reference safety information (RSI) (the relevant summary of product characteristics for each IMP). SAEs that are deemed to be unexpected and related to the intervention will be deemed Suspected Unexpected Serious Adverse Reactions (SUSARs) and will be notified to the research ethics committees (REC), Medicines and Healthcare Regulatory Authority (MHRA) and sponsor within the relevant deadline. All such events will be reported to the Sponsor, TSC and DMC at their next meetings.

AEs that relate specifically to allergic sensitisation sub-study procedures will be recorded from the time of the allergy clinic appointment until 5 days thereafter. AEs that relate specifically to biological sampling procedures will be recorded from the time of the baseline blood sample until 24 h after the second blood sample has been collected.

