## Allergic sensitisation substudy

### Baseline blood sampling and processing

Where possible, 10 mL of blood will be taken following induction of anaesthesia and prior to the administration of the IMP (either pre- or post-randomisation). Where this is not possible, the blood sample will be taken as close as possible to IMP administration. The samples will be processed in the hospital laboratory, frozen, and stored. Samples will be transported in batches to the immunology laboratory at Leeds Teaching Hospitals NHS Trust, at a time of mutual convenience, where mast cell activation testing will be performed. Any samples not used will be disposed of in accordance with local policy and applicable regulations.

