### Follow-up testing at 6 weeks to 6 months

Following baseline blood sampling, and depending on group allocation, participants will undergo a clinical assessment, comprising review of notes and/or telephone or face-to-face consultation by an allergy specialist. This assessment will determine suitability for skin testing. Participants will be asked to attend a local drug allergy clinic between 6 weeks and 6 months after their surgery for repeat blood sampling (for mast cell activation) and, if appropriate, a skin test. In line with routine drug allergy skin testing clinics, some medications may be discontinued for a period of one week prior to testing. Where appropriate in the clinical judgment of the allergy specialist, skin testing will be performed at an allergy clinic. This comprises skin prick and intradermal testing on the forearm of both arms, each test 2 cm apart. Positive and negative control tests will be performed on the forearm using histamine and saline respectively prior to skin prick testing, to ensure that the patient’s skin is appropriately reactive. A negative control saline intradermal test will be performed prior to intradermal testing, to confirm appropriate skin reactivity. The testing takes around one hour in total and involves minor discomfort from the slight scratching of the skin with each test. Any skin test developing a wheal of 3 mm or greater than the negative control site is usually considered positive, but the result of the test is a clinical judgment of the allergy specialist. Systemic reactions to skin testing are rare but can occur, typically involving urticaria and a sensation of itch, although more severe allergic reactions are possible. The testing will be performed by specialists who are trained and experienced in the conduct and management of skin testing, and who will treat any symptoms which occur in line with local and national guidance. The patient will be contacted between 48 h and one week following testing to check whether any of the test sites developed localised redness or swelling, which indicates a possible delayed-type allergic reaction. In line with standard drug allergy testing procedure, patients may be offered a drug provocation test, whereby they are given small doses of sugammadex in a carefully monitored setting at the earliest practical opportunity. This is both for future safety of the patient and to understand the specificity of skin testing.

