## Plans for collection, laboratory evaluation and storage of biological specimens for genetic or molecular analysis in this trial/future use {33}

In selected study sites, biological samples will be collected which will be stored for future analysis as part of a separate research programme aiming to understand biological phenotypes in the perioperative period. This work will be subject to separate ethical approval and separate funding application(s). With patient consent, 30 mL blood samples (approximately) will be taken on two occasions: at baseline (any time between consent and the beginning of the surgery) and on post-operative day 1 at 12–24 h following the end of surgery or as close as possible. This will be processed according to a specified standard operating procedure. Samples will be transferred in batches, at a time of mutual convenience, to a laboratory at Queen’s University Belfast for analysis and storage for future use. If a patient is enrolled but not randomised, sampling and data collection will proceed unless the patient is specifically withdrawn from the substudy.

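### Adverse events in the week when medication may be stopped before allergy testing fall outside every recording window the protocol states

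*Protocol article*

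**What the plan says.** The section on adverse event reporting and harms {22} of the protocol article sets three recording windows.

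- General, for all participants: "All AEs and SAEs will be recorded from the time of IMP administration until 24 h thereafter".
- Allergy substudy: "AEs that relate specifically to allergic sensitisation sub-study procedures will be recorded from the time of the allergy clinic appointment until 5 days thereafter".
- Sampling: "AEs that relate specifically to biological sampling procedures will be recorded from the time of the baseline blood sample", ending 24 hours after the second sample.

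The section on follow-up testing at 6 weeks to 6 months has substudy participants "attend a local drug allergy clinic between 6 weeks and 6 months after their surgery for repeat blood sampling" and, where the allergy specialist thinks it appropriate, for skin testing. In preparation, "some medications may be discontinued for a period of one week prior to testing". The protocol presents this as ordinary practice in drug allergy clinics.

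The substudy's first blood sample is described under baseline blood sampling and processing. The preferred arrangement is that "10 mL of blood will be taken following induction of anaesthesia and prior to the administration of the IMP"; otherwise it is taken as near to drug administration as can be managed.

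**The concern.** A window for harms of a procedure should open no later than the first step that could cause harm. Here the protocol names a preparatory step, stopping medication for a week, and then starts recording at the visit that ends that week.

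Participants are aged 50 or older, had major surgery within the preceding months and, according to the Discussion, often have other illnesses. They are asked to attend because they agreed to an optional substudy (consent provisions {26b}). For them, an event caused by the stop arises from taking part in research. The same section {22} states that the potential risk to participants does not exceed that of standard care. For this step the recorded data could not support or contradict that statement.

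**Working it through.** The plan gives no figure to reproduce. The check places each stated window and each substudy step on one time axis.

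**Inputs** (day 0 = surgery and trial drug; T = day of the clinic appointment, assumed to be the day of testing)

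- Clinic visit: 6 weeks to 6 months after surgery, so the earliest T = 6 × 7 = 42 (follow-up testing section).
- Medication stop: one week before testing, from T − 7 to T (same section).
- General window: day 0 to day 1 (section {22}).
- Substudy window: T to T + 5 (section {22}).
- Sampling window: first sample to 24 hours after the second, for sampling-related events only (section {22}).

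**Does any window cover T − 7 to T?**

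1. *Substudy window.* It opens at T, so none of the preceding 7 days is inside it.
2. *General window.* It closes at day 1. The earliest stop is T − 7 = 42 − 7 = day 35, which is 35 − 1 = 34 days after the window closed. A later visit widens the gap.
3. *Sampling window.* There are two readings. If it means only the samples stored for future research, taken at baseline and post-operative day 1 (section {33}), it ends about a day after the second of them, long before day 35. If it also means the substudy's own samples, the second of these is the repeat sample at the clinic, and the window spans the medication-stop week in calendar time. Even then it admits only events related to sampling, and an effect of stopping a medicine is not one.

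On either reading, up to 7 days of medication withdrawal lie in no window that would record an event it caused.

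**The day-0 substudy sample, checked the same way.** It is taken next to drug administration. Any event present or noticed in the following 24 hours is in the general window, which records all events whatever their cause. On the wider reading the sampling window covers the sample as well. What could be missed is the short interval between sample and drug, or a participant who is sampled but never given the drug, and only if the sampling window is read narrowly.

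**How many are exposed.** The substudy recruits up to 250 (sample size section {14}). Exposure requires both being judged suitable for skin testing and taking a medicine that is stopped. The protocol gives neither proportion, so the number lies somewhere between 0 and 250 and cannot be narrowed from the document.

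**The case against.** The best case for leaving the text alone has four parts.

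*The stop is routine clinic practice, and where a procedure-specific window opens is partly a design choice.* This has some force, but the visit itself happens because of the substudy, and no reason is given for starting the record after the preparation.

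*The article condenses a fuller protocol, which may have the clinic ask about the preceding week.* That would be an answer if the article were silent. It is not silent: it fixes a start time, and that start time is later than a step it describes itself.

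*Other routes exist.* Section {22} also asks investigators to record events that clinical or research teams consider relevant to the trial, and health resource use is collected over 180 days. So it would be too strong to say that such an event could never be recorded, and one still present at the appointment could be noted. Neither route sets a window for this week, however, and resource use does not attribute cause.

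*The consequence is limited.* This stands. A reader might infer from the Discussion's interest in the best testing pathway that a reported harm rate for that pathway will be too low. The outcomes section {12} lists no such outcome: the substudy reports sensitisation and the correlation between tests. No prespecified estimate is shown to be biased.

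Two other strong readings are tempting. One is that harms from the first blood sample also go unrecorded; the general window, and possibly the sampling window, answer that. The other is that the protocol treats equivalent procedures unequally by opening the sampling window at the first sample. The future-use sample may be taken at any time between consent and the start of surgery, so it has its own reason for an early start.

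**Conclusion.** The point holds for the medication-stop week. The follow-up testing section and section {22} do not fit together, and an event that starts and resolves in that week would not be captured as a substudy adverse event. The size is up to 7 days per exposed participant, beginning at the earliest about day 35 after surgery. This assumes that testing takes place at the clinic appointment and that the stop lasts the full week.

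Two numbers should not be drawn from this. A reader might set 7 unrecorded days against 5 recorded ones and report 7/12 = 58% as missed, but that is a share of days, and nothing in the protocol suggests equal risk before and after testing. A reader might also take 250 as the number affected, but that is the recruitment ceiling.

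This is a modest gap in safety recording. It does not affect the primary comparison or any listed substudy outcome. It is worth correcting because the step arises from optional research participation and the correction is cheap.

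**What to change.** Reconcile the two sections. Open the substudy adverse event window when a participant is told to stop any medicine for testing, or at the appointment if nothing is stopped. At the appointment, ask about events since that instruction and record them.

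As a secondary clarification, state whether the sampling window covers the substudy's day-0 sample as well as the samples stored for future use.

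The main change costs one protocol sentence and one case report form question, with a small recall burden at the visit. The clarification needs a phrase. Only recording changes; nothing is proposed about which medicines are stopped or for how long.

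### Adverse-event recording for the allergy substudy ends 5 days after the clinic appointment, but the planned check for delayed reactions may run to one week, and the window for a later provocation test is not stated

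*Protocol article*

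**What the plan says.** The protocol article, under Adverse event reporting and harms {22}, sets three recording windows:

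- Main trial: "All AEs and SAEs will be recorded from the time of IMP administration until 24 h thereafter".
- Allergy substudy procedures: events "will be recorded from the time of the allergy clinic appointment until 5 days thereafter".
- Biological sampling procedures: from the baseline sample "until 24 h after the second blood sample has been collected".

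Under Follow-up testing at 6 weeks to 6 months, the article describes the clinic visit (repeat blood sample and, if appropriate, skin testing) and then a safety contact: "The patient will be contacted between 48 h and one week following testing". Its purpose is to find late skin changes where the tests were placed, which the article treats as a sign that a delayed reaction may have occurred. On skin testing it notes that systemic reactions are rare, "although more severe allergic reactions are possible". Some patients may then be offered a provocation test, in which they are "given small doses of sugammadex in a carefully monitored setting at the earliest practical opportunity". No day is fixed for that test, and the harms section does not mention it.

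**The concern.** One section tells sites to look for delayed reactions for up to a week. Another closes the period in which such reactions are recorded as adverse events at 5 days. A site can follow the substudy section exactly, telephone on day 7, learn of a reaction that began on day 6, and have no stated basis for entering it as an AE.

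The provocation test raises a related question. It is a deliberate re-exposure to the drug under suspicion, and its date is open. The substudy window starts at the clinic appointment, which the substudy section describes as the visit for blood sampling and skin testing.

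Entry as an AE or SAE is what starts the assessment of severity and causality and, for SAEs, of expectedness, with onward reporting to the regulator, ethics committee, sponsor and oversight committees where required. An event outside the window may not enter that chain. The article presents the substudy as a guide to the allergy testing pathway, so the harms of that pathway should be recorded over the period in which the protocol itself looks for them.

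**Working it through.** There is no power or sample-size figure to reproduce. The check compares the stated time windows. Day 0 is the clinic appointment, and testing is assumed to take place that day.

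**Inputs**

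- AE window for substudy procedures: day 0 to day 5 (Adverse event reporting and harms {22}).
- Post-test contact: 48 h to one week, so day 2 to day 7 (Follow-up testing at 6 weeks to 6 months).
- Provocation test: day d, not fixed (same section).
- Substudy size: up to 250, of whom 200 will have received sugammadex and 50 neostigmine (Sample size {14}).

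**Contact period against AE window**

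- Length of contact period: 7 − 2 = 5 days.
- Part inside the AE window: 5 − 2 = 3 days.
- Part after the AE window closes: 7 − 5 = 2 days.
- Share after closure: 2 / 5 = 40%.

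The 40% is a share of calendar time. It does not estimate the proportion of reactions missed, because the article gives no data on time to onset.

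**Provocation test, if it does not open its own window**

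- Recording time left after a test on day d, for d from 0 to 5: 5 − d days. A test on day 3, for example, leaves 5 − 3 = 2 days.
- A test with d greater than 5 leaves none.

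**Could another window cover the gap?**

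- The main-trial window ends 24 h after IMP administration, whereas the clinic visit comes 6 weeks to 6 months after surgery. Criteria for discontinuing or modifying allocated interventions {11b} describes the intervention as given at a single point in time. Even if a challenge dose counted as IMP, 24 h would not reach delayed-type reactions.
- The sampling window covers sampling procedures only. The section on biological specimens {33} places those samples at baseline and post-operative day 1. Even if the clinic blood sample counted as the second one, that window would close 24 h later, before the 5-day window does.

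Neither window covers a skin-test reaction that starts on day 6 or 7.

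**The case against.** The strongest reply is that the two windows measure different things: one says when the patient is asked, the other which events are recorded. A day-7 call looks back and can pick up a reaction that began on day 3. That stands. A contact later than the end of the recording window is not a contradiction in itself, and the gap concerns only reactions that start after day 5. The article does not say whether its window refers to onset or to report. If it refers to report, the gap is wider.

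Second, a reader might infer that the substudy's own results are lost. The documents do not support this. Outcomes {12} lists positive skin test and positive challenge test as outcomes, and the contact exists to find delayed site reactions. The AE window does not limit outcome collection. What is at risk is AE/SAE classification and causality assessment.

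Third, a reader might infer that a provocation test on another day has no AE recording at all. That goes too far. The harms section does not restrict the clinic appointment to the skin-test visit, so a provocation visit could count as a further appointment with its own 5 days. Even on the narrow reading, a test on days 1 to 4 keeps some recording time. What stands is that the text does not settle the matter.

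Fourth, these procedures are not all purely for research: the article says provocation also serves the patient's future safety. Nor are 250 people exposed to the gap. That number is a recruitment ceiling, skin testing depends on the allergy specialist's judgement, and provocation is only offered to some.

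Finally, this is a condensed article, and the full protocol may define the appointment and the handling of provocation visits. That tempers the provocation point. It does not remove the 5-day against one-week mismatch, because the article states both figures.

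**Conclusion.** The point holds in limited form. AE recording for substudy procedures closes at day 5, while the planned contact for delayed reactions may run to day 7. Reactions that start in the last 2 of the contact period's 5 days can be detected yet fall outside AE/SAE recording and causality assessment. This assumes that testing takes place at the appointment and that the window refers to onset.

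The provocation limb is conditional: if a test on a later day does not open its own window, one held more than 5 days after the appointment has no AE recording.

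The number of events affected cannot be estimated from the document. The effect is on safety capture in the tested subset of up to 250 participants. DAH-30, the main treatment comparison and the collection of skin-test and challenge results are untouched.

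**What to change.** Reconcile Adverse event reporting and harms {22} with Follow-up testing at 6 weeks to 6 months, so that AE recording for substudy procedures runs at least to the end of the planned post-test contact period. State whether the window refers to onset or to report. State that a provocation test on a separate day opens its own AE recording window. These changes concern recording only and alter no clinical procedure.

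The cost is a wording change in the safety section, a matching change to the substudy CRF, and slightly longer recording. No extra visits or contacts are needed, since the one-week contact is already planned.
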